**4.3.5 - Tomographic Orders**

Once clinical data has been entered into the computer, tomographic request will be generated. These requests will be printed on the radiographic forms or computer systems currently in use at each institution.

**4.3.5.1 - Radiographic Imaging**

**4.3.5.1.1 - Radiographic Evaluation**

All patients entered into the main study will initially undergo computed head tomography. Cases will be excluded from the study if the tomography is incomplete and all scan slices are negative. Initial tomography may be supplemented by plain radiographs, additional tomography, angiography or any other imaging study deemed necessary by either ED physicians, neurosurgeons, or radiologists.

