**4.3.5.1.2 - Injury Diagnosis**

All radiographs will be reviewed by clinical radiologists at the individual study centers, who will be unaware of the patient’s classification by the decision rule. The diagnosis of significant intracranial injury will be based on final radiological interpretation of emergency department studies as well as any additional studies performed in the in-patient setting. Cases for which the initial diagnosis of “intracranial injury” or “no intracranial injury” proves incorrect will be reclassified to the appropriate group.

Copies of final computed head tomography readings will be collected on every patient in the study. The collected reports will include the final readings of every computed head tomography procedure performed on every patient. These reports will be collected on a weekly basis. Each report will be abstracted to determine whether a significant intracranial injury was detected by the procedure. Additional radiological studies of the head (magnetic resonance imaging, angiography, etc.) will also be collected and abstracted to ascertain which modalities produced diagnostically specific information. Final diagnoses of significant intracranial injury will be made on the basis of these reports and the need for neurosurgical intervention. In the event of ambiguous reports, [name] will review all of the available radiological studies and make a final determination of injury status. Data abstracted from each report will be concatenated with the computer survey data to form the final study database.

For operational purposes, a patient will be considered to have a positive computed tomogram if they exhibit any of the following findings [72]:

Mass effect or sulcal effacement

Signs of herniation

Basal cistern compression or midline shift

Extensive subarachnoid hemorrhage

Significant epidural or subdural hematomas (greater the 1.0 cm in width, or causing mass effect)

Significant cerebral contusion (more than 1.0 cm in diameter, or more than one site)

Hemorrhage in the posterior fossa

Intraventricular hemorrhage

Bilateral hemorrhage of any type

Depressed or diastatic skull fracture

Pneumocephalus

Diffuse cerebral edema

Diffuse axonal injury

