Injuries such as isolated linear or basilar skull fractures, solitary small cerebral contusions, localized subarachnoid hemorrhage less than 1 mm thick, thin subdural hematomas less than 4mm thick, isolated pneumocephaly, and closed depressed skull fractures that do not violate the inner table will not be considered to be significant injuries [63]. Coincidental or congenital abnormalities will also not be considered to be significant intracranial injuries. Chronic subdural hematomas, without evidence of acute change, will be considered to be coincidental injuries and will not be considered to be significant acute injuries. Chronic subdural hematomas that exhibit any recent change, or those that are of indeterminate age, will be considered to be acute significant injuries.

Research assistants, blind to classification by the decision rule, will review the medical records of patients with positive tomographic scans to determine whether or not the patient received neurosurgical intervention. The need for neurosurgical intervention is defined as any of the following within seven days of the initial injury [63]:

1 – Death due to intracranial injury.

2 – Intubation for management or support of head injury.

3 – Craniotomy, elevation of skull fracture or intracranial pressure monitoring.

Cases involving death or intubation will be reviewed by the physician liaison to determine, on the basis of their best clinical judgment, whether there was a causal relationship between the event and the patients intracranial injury. The liaisons will be instructed to consider these events as causally related to intracranial injury unless there is compelling evidence to the contrary. Patients will not be considered to have received neurosurgical intervention if their death is clearly due to causes unrelated to their head injury, or if they were intubated solely to expedite care.

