**4.3.7 - Data Analysis**

The primary outcome for the study is the point measure and associated 95% confidence interval for the sensitivity of the decision instrument in identifying patients who require neurosurgical intervention. Additional operator characteristics of interest for this population include the negative predictive value and specificity. Secondary outcomes include the sensitivity, negative predictive value and specificity of the instrument in detecting patients who harbor clinically significant intracranial injuries as described by the criteria defining positive CT imaging (see 4.3.5.1.2 - Injury Diagnosis above). A further secondary goal of the study is to determine and compare the operator characteristics of both the NEXUS head CT instrument, as well as both forms (“high risk” and “medium risk”) of the Canadian head CT instrument, among patients who meet the inclusion and exclusion characteristics for classification by the Canadian rules.

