**4.3.8.2 - Protection of Radiographic Data Integrity**

Preliminary diagnoses of "no injury" will be confirmed in two ways. First, quality assurance logs, which contain lists of significant radiological findings that were missed on preliminary reading, will be reviewed by the site liaisons during routine evaluations. Any revisions found on these surveys will be transmitted to UCLA where they will be incorporated into the study database. Second, the diagnoses of all blunt trauma patients admitted through the emergency department and discharged from the hospital during and up to three months after each study period will be searched and all intracranial injury cases identified. The charts of such patients will be reviewed to determine if the case was included in the study (using the patient number previously printed on the redacting forms), and if so, whether the case was classified as having an intracranial injury (based on whether the leaf was marked). The liaisons will notify core UCLA personnel of any cases of missed injury detected in this fashion. These cases will be reviewed by the site liaisons to determine, based on their best judgment, whether they involve protocol errors, and whether they represent a false-negative event (patient with a head injury, but “low-risk” according to the decision instrument). Site coordinators will notify core UCLA personnel of their findings. Reviews of the quality assurance logs and discharge diagnoses will be performed by the site liaisons on a bi-monthly basis.

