**Appendix C – Detailed Description of Criteria Included in the NEXUS Head CT Instrument**

Terms are defined for purposes of clarity and to ensure consistent data collection.

*Evidence of skull fracture includes* signs of *basilar skull fracture* (including, but are not limited to) periorbital or peri-auricular ecchymoses, hemotympanum, and drainage of clear fluid from the ears or nose. Signs of *depressed or diastatic skull fracture* include a palpable step-off of the skull, a stellate laceration from a point source, or any injury produced by an object striking a localized region of the skull (such as a baseball bat, club, pool cue, golf-ball, baseball, pipe, etc.).

*Scalp hematoma* refers to swelling secondary to hematoma formation over any portion of the bony calvarium. Injuries that do not involve the calvarium, including hematomas limited to the face and neck are not considered scalp hematomas.

*Neurologic deficit* refers to any abnormal neurologic finding revealed by detailed testing. This may include motor or sensory deficits (abnormal weakness or sensation in any one or more of the four extremities, as determined by systematic testing of muscle strength and sensation in all four limbs), cranial nerve abnormality (particularly cranial nerves II-XII, as determined by systematic testing of each nerve), cerebellar abnormality as manifest by ataxia, dysmetria, dysdiadokinesis, or other impairment of cerebellar function (as determined by systematic testing of cerebellar function, including tests of ataxia, and finger-nose-finger, heel-to-shin, and rapid alternating movements), gait abnormality or inability to walk normally (may be due to inadequate strength, loss of balance or ataxia; it is determined by systematic testing of gait, including tandem and heel-to-toe walking, and Romberg testing), or any other impairment of neurological function.

*Abnormal level of alertness* is evidenced by a variety of findings, including but not limited to a Glasgow coma score of 14 or less; delayed or inappropriate response to external stimuli; excessive somnolence; disorientation to person, place, time or events; inability to remember three objects at five minutes; perseverating speech; and other neurological impairments.

*Abnormal behavior* is any inappropriate action displayed by the victim. It includes such things as excessive agitation, inconsolability, refusal to cooperate, lack of affective response to questions or events, and violent activity.

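### Incomplete scans are excluded only when every slice is negative, so inclusion depends on the index CT result and a missed neurosurgical case could drop out of a primary analysis that tolerates no miss

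*Protocol*

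**What the plan says.** Section 4.3.5.1.1 of the Protocol sets the rule: "Cases will be excluded from the study if the tomography is incomplete and all scan slices are negative". It goes on: "Initial tomography may be supplemented by plain radiographs, additional tomography, angiography or any other imaging study deemed necessary". It does not say whether such later imaging lifts the exclusion.

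Section 4.3.7 makes the primary outcome the "sensitivity of the decision instrument in identifying patients who require neurosurgical intervention". Section 4.3.5.1.2 defines that need as death due to intracranial injury, intubation for the head injury, or a listed procedure (craniotomy, elevation of a skull fracture, or intracranial pressure monitoring) within seven days of injury.

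Three other provisions bear on the point:

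- **Reclassification (4.3.5.1.2).** An initial diagnosis that "proves incorrect will be reclassified to the appropriate group". Excluded cases are not mentioned.
- **Record review (4.3.5.1.2).** Research assistants "will review the medical records of patients with positive tomographic scans to determine whether or not the patient received neurosurgical intervention". Section 4.3.4 has the same condition: records are opened if the CT report shows an intracranial injury.
- **Discharge search (4.3.8.2).** Discharge diagnoses are searched up to three months after each study period. "The charts of such patients will be reviewed to determine if the case was included in the study".

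**The concern.** Two patients with the same interrupted scan are handled differently according to what the available slices show. A reference-standard result is therefore deciding who is in the study.

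For the primary outcome this is avoidable, because the seven-day event is clinical and can be read from the hospital record whether or not the first CT was finished. The patient who matters has none of the criteria, a truncated scan with only negative slices, and then one of the listed events. That patient is a false negative of the instrument. Under the wording of 4.3.5.1.1 the case may leave the study. It would then not count against sensitivity, nor towards the ten-miss termination rule in section 4.3.10.3.

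Two other sections show why this deserves attention. Section 4.3.9.1 claims that the enrolment method captures everyone who is scanned, and section 4.3.9.2 itself names non-random exclusion as a source of bias in specificity.

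**Working it through.** **Inputs from the Protocol**

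- Target lower limit 0.99, α = 0.05 with α/2 in the exact limit, and 368 neurosurgical cases with no miss (section 3.2)
- Prevalence 1.2% and about 31,000 patients (section 3.2)
- Derivation cohort: 13,728 patients, 917 injured, 1,752 true negatives, specificity 13.7% (section 3.1)
- Rate of incomplete scans: not given

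**1. Reproduce the plan's figure.** With X = N, the exact lower limit is (α/2)^(1/N).

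- N = 367: 0.025^(1/367) = 0.989999, just short of 0.99
- N = 368: 0.025^(1/368) = 0.990026

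So 368 is the smallest N that reaches 0.99, as stated. 368 / 0.012 = 30,667, which agrees with about 31,000.

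**2. Effect of one miss on the primary result.** Exact two-sided 95% lower limits:

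| Situation | Result | Lower limit |
|---|---|---|
| Missed case excluded, 368 others all detected | 368/368 | 99.00% |
| Missed case kept as one of 368 | 367/368 | 98.50% |
| Missed case kept as an additional case | 368/369 | 98.50% |

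With one miss, 555 neurosurgical cases would be needed for a lower limit of 99.0%.

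**3. How likely is an excluded miss?** Assume 0.5% to 3% of scans are incomplete, independently of criterion status, and that one miss is expected among 368 cases. The expected number of excluded misses is then at most 1 × 0.005 = 0.005 to 1 × 0.03 = 0.03. It is lower still because every available slice must also be negative.

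**4. Effect on specificity.** Uninjured patients in the derivation cohort: 13,728 − 917 = 12,811. Of these, 12,811 − 1,752 = 11,059 were criterion-positive, and 11,059 / 12,811 = 86.3%.

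Let s be the specificity without exclusions, r the fraction of uninjured patients excluded, and c the share of those who are criterion-positive. Reported specificity = [s − r(1 − c)] / (1 − r). With s = 0.137:

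- c = 0.863, any r: 0.137(1 − r)/(1 − r) = 13.7%, so no bias
- c = 1, r = 0.005: 0.137/0.995 = 13.8%, about 0.1 points high
- c = 1, r = 0.03: 0.137/0.97 = 14.1%, about 0.4 points high

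The values of r and c are assumptions. The 13.7% refers to clinically important injury, not to neurosurgical need, so it serves only as a guide to size for the primary-outcome specificity.

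**5. Can the case be recovered?** Read side by side, section 4.3.5.1.1 permits further imaging, section 4.3.5.1.2 corrects injury status, and section 4.3.8.2 checks discharged patients against the study list. None of the three says that a case excluded for an incomplete negative scan returns. A patient who dies or is intubated without repeat imaging would stay excluded even if repeat imaging did restore cases.

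**The case against.** The strongest defence is that a partial scan can show an injury but cannot rule one out, so dropping indeterminate negatives has a rationale. Section 4.3.5.1.2 also collects every head CT on every patient and bases the diagnosis on later in-patient studies too. A re-scanned patient could naturally be read as having complete tomography and staying in. The sheet used for matching in the discharge search is printed with the imaging request, before the scan (section 4.3.4), so an interrupted-scan patient admitted with intracranial injury might be found. All of this is reasonable, but none of it is written down, and it does not cover a patient who has the event without repeat imaging.

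Some stronger readings are tempting, and the documents do not support them:

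- **The rule contradicts the reclassification provision.** "Cases for which the initial diagnosis of “intracranial injury” or “no intracranial injury” proves incorrect will be reclassified to the appropriate group" can be read as applying only to cases that remain in the study. The relation between the two sections is ambiguous, not contradictory.
- **The primary outcome is already known for these patients.** It is not routinely known, because records are reviewed only after a positive scan.
- **Specificity is materially inflated.** Appendix C counts uncooperative behaviour as a criterion ("It includes such things as excessive agitation, inconsolability, refusal to cooperate"), so a reader might infer that interrupted scans come mostly from criterion-positive patients. The Protocol does not say why scans are interrupted, and 86.3% of uninjured patients are criterion-positive anyway. Only an excess over that share biases specificity. An excluded criterion-positive patient who needs neurosurgery is a lost true positive, not a hidden miss.

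Section 4.3.9.1 argues that injuries missed on standard CT are irrelevant. That does not answer the point, because a truncated scan has not examined the whole head.

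**Conclusion.** The point holds in a limited form. The exclusion depends on the index scan result, it is not needed for the primary outcome, and it leaves a route by which a missed neurosurgical case can leave the analysis.

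A reader might go further and infer that the rule does hide misses. The documents do not support that: none of the 16 injuries missed in the derivation study needed neurosurgery, no rate of incomplete scans is given, and under the assumptions in the working the expected number of excluded misses is 0.03 or less. The concern is that the consequence is large if it happens once. If the remaining cases contain no miss, one such exclusion moves the exact lower limit from 98.5% to 99.0%, which is the difference between failing and meeting the plan's own target.

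The effect on specificity is secondary: between zero and about 0.4 percentage points for up to 3% incomplete scans and a criterion-positive share of 86.3% or more among the uninjured patients excluded.

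**What to change.** Replace the exclusion sentence in section 4.3.5.1.1 with a rule that covers five things:

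- An incomplete initial scan is not a reason for exclusion.
- A later complete study replaces the incomplete one for the CT outcome.
- The seven-day record review in section 4.3.5.1.2 is extended to all patients with an incomplete scan, and the primary outcome is classified from the record. Keeping the patients without this step is not enough: with no positive scan there would be no review, and a low-risk patient who had the event could be counted as a true negative.
- If no complete study exists, the CT outcome is indeterminate, and the CT-based measures are shown with these patients counted once as injured and once as uninjured.
- The number of incomplete scans is reported by instrument result.

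The condition in section 4.3.4 for opening the medical record needs the same extension. The cost is a change of wording, a small number of additional chart reviews and some added lines of analysis. The estimates may be slightly less favourable.

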**4.3.5.1.2 - Injury Diagnosis**

All radiographs will be reviewed by clinical radiologists at the individual study centers, who will be unaware of the patient’s classification by the decision rule. The diagnosis of significant intracranial injury will be based on final radiological interpretation of emergency department studies as well as any additional studies performed in the in-patient setting. Cases for which the initial diagnosis of “intracranial injury” or “no intracranial injury” proves incorrect will be reclassified to the appropriate group.

Copies of final computed head tomography readings will be collected on every patient in the study. The collected reports will include the final readings of every computed head tomography procedure performed on every patient. These reports will be collected on a weekly basis. Each report will be abstracted to determine whether a significant intracranial injury was detected by the procedure. Additional radiological studies of the head (magnetic resonance imaging, angiography, etc.) will also be collected and abstracted to ascertain which modalities produced diagnostically specific information. Final diagnoses of significant intracranial injury will be made on the basis of these reports and the need for neurosurgical intervention. In the event of ambiguous reports, [name] will review all of the available radiological studies and make a final determination of injury status. Data abstracted from each report will be concatenated with the computer survey data to form the final study database.

For operational purposes, a patient will be considered to have a positive computed tomogram if they exhibit any of the following findings [72]:

Mass effect or sulcal effacement

Signs of herniation

Basal cistern compression or midline shift

Extensive subarachnoid hemorrhage

Significant epidural or subdural hematomas (greater the 1.0 cm in width, or causing mass effect)

Significant cerebral contusion (more than 1.0 cm in diameter, or more than one site)

Hemorrhage in the posterior fossa

Intraventricular hemorrhage

Bilateral hemorrhage of any type

Depressed or diastatic skull fracture

Pneumocephalus

Diffuse cerebral edema

Diffuse axonal injury

Injuries such as isolated linear or basilar skull fractures, solitary small cerebral contusions, localized subarachnoid hemorrhage less than 1 mm thick, thin subdural hematomas less than 4mm thick, isolated pneumocephaly, and closed depressed skull fractures that do not violate the inner table will not be considered to be significant injuries [63]. Coincidental or congenital abnormalities will also not be considered to be significant intracranial injuries. Chronic subdural hematomas, without evidence of acute change, will be considered to be coincidental injuries and will not be considered to be significant acute injuries. Chronic subdural hematomas that exhibit any recent change, or those that are of indeterminate age, will be considered to be acute significant injuries.

Research assistants, blind to classification by the decision rule, will review the medical records of patients with positive tomographic scans to determine whether or not the patient received neurosurgical intervention. The need for neurosurgical intervention is defined as any of the following within seven days of the initial injury [63]:

1 – Death due to intracranial injury.

2 – Intubation for management or support of head injury.

3 – Craniotomy, elevation of skull fracture or intracranial pressure monitoring.

Cases involving death or intubation will be reviewed by the physician liaison to determine, on the basis of their best clinical judgment, whether there was a causal relationship between the event and the patients intracranial injury. The liaisons will be instructed to consider these events as causally related to intracranial injury unless there is compelling evidence to the contrary. Patients will not be considered to have received neurosurgical intervention if their death is clearly due to causes unrelated to their head injury, or if they were intubated solely to expedite care.

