**4.2 Protocol Overview**

Emergency physicians working in affiliated study centers will collect survey data on all blunt head trauma victims undergoing computed head tomography. In stable patients, survey data will be collected prior to radiographic imaging. In unstable patients, clinicians will be expected to complete data collection without delaying patient care, whenever possible, and will formulate answers to data questions, even if not recorded, prior to radiographic review. Tomographic imaging of individual patients will be performed only after data collection is complete and a radiographic request has been issued. Radiographic requests will only be available after a complete data form has been submitted.

Information collected on each patient will include demographic information, select elements of history and physical examination and results of computed head tomography. Data from each study center will be captured and stored on a computer database for eventual concatenation with data from other centers.

All radiographic studies will be reviewed by clinical radiologists at each participating center. Injury determination and classification will be based on final radiological findings. Injury type and location will be recorded for all patients having significant head injuries. The hospital records of patients who have positive CT imaging will be reviewed to ascertain whether their injuries required neurosurgical intervention. Radiographic diagnoses and need for neurosurgical intervention will then be concatenated with survey data on a case-by-case basis to form the final study database.

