Study index numbers will be used to link radiographic results and the need for neurosurgical intervention to survey data. This can be accomplished in a manner identical to that used in our earlier studies using the following procedure. At the time a radiographic request is printed, an additional sheet is printed. The upper left corner of the sheet contains the patient’s medical record number, while the lower corner of the sheet contains the study index number. These sheets will be collected by site coordinators. By examining the upper left hand corner of each page, the coordinators will know which radiographic studies to retrieve. Once the radiographic study has been collected for a patient, the regional coordinators will place the lower right hand corner of the study sheet (containing the study index number) over the patient identifying information on the tomography report. The tomography report will then be photocopied with the study index number covering all identifying patient data, thus effectively redacting all identifying information from the tomography report. If the tomography report reveals an intracranial injury, the patient’s medical records for the associated visit will be reviewed, and the redacted tomography report will be modified by including a notation regarding the need, if any, for neurosurgical intervention. The redacted photocopies will then be forwarded to UCLA. Once the tomographic reports and need for neurosurgical intervention have been collected, redacted and photocopied, the sheets containing both patient medical record and study number will be cut in half to yield a one leaf with patient medical record number, and a separate leaf with the study index number. A mark will be placed on the leaf containing the patient medical record number of any patient requiring neurosurgical intervention. The study index numbers will be destroyed, while the medical record numbers will be retained for quality assurance reviews (see below). All sheets will be destroyed on study completion.

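### The CT outcome definition in 4.3.5.1.2 contradicts itself, and the record review that establishes the primary outcome is triggered in two different ways

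*Protocol*

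**What the plan says.** **CT outcome (protocol 4.3.5.1.2).** The operational rule is that "a patient will be considered to have a positive computed tomogram if they exhibit any of the following findings". The list includes "Depressed or diastatic skull fracture", "Pneumocephalus", "Significant epidural or subdural hematomas (greater the 1.0 cm in width, or causing mass effect" and "Extensive subarachnoid hemorrhage", and also posterior fossa hemorrhage and bilateral hemorrhage of whatever type. The next paragraph gives injuries that do not count: "isolated pneumocephaly, and closed depressed skull fractures that do not violate the inner table will not be considered to be significant injuries". The same sentence removes subdurals under 4 mm and localized subarachnoid blood under 1 mm thick. The two paragraphs cite different sources.

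**Use of the definition (4.3.7).** The secondary outcomes are the sensitivity, negative predictive value and specificity for clinically significant injury, defined by the positive-CT criteria. The primary outcome is sensitivity for patients who need neurosurgical intervention. Section 4.3.5.1.2 defines that need as death from intracranial injury, intubation for head injury, or specified procedures, within seven days of injury.

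**Record review.** Section 4.2 states: "The hospital records of patients who have positive CT imaging will be reviewed to ascertain whether their injuries required neurosurgical intervention". Section 4.3.5.1.2 likewise has blinded research assistants review patients with positive scans. Section 4.3.4 uses a wider condition, "If the tomography report reveals an intracranial injury", and then refers to the records of the associated visit.

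**The concern.** There are two linked problems.

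First, positive CT and significant injury are meant to be one outcome, yet some findings are positive under one paragraph and not significant under the next. The secondary estimates then depend on which paragraph the abstractor follows. If sites abstract differently, a later analysis plan cannot recover what was recorded inconsistently.

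Second, the need for neurosurgery is learned by opening the record, and the sections disagree about whose record is opened. Take a patient with a 6 mm subdural and no mass effect. The scan is not positive under the list, so 4.2 and 4.3.5.1.2 do not call for review; 4.3.4 does. If such a patient met the primary outcome, was low risk by the instrument, and was not found, the case would be counted as a true negative instead of a miss. The study stops at 368 neurosurgical cases or 10 misses (4.3.10.3), so the same ascertainment also drives both stopping counts.

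**Working it through.** **Step 1: the two paragraphs of 4.3.5.1.2 side by side.**

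| Finding | Positive-CT list | Not-significant paragraph | Result |
|---|---|---|---|
| Isolated pneumocephalus | Positive, no exception | Not significant | Contradiction |
| Closed depressed fracture, inner table intact | Positive, no exception | Not significant | Contradiction |
| Subdural under 4 mm, bilateral or in the posterior fossa | Positive | Not significant | Contradiction |
| Subdural under 4 mm, otherwise, no mass effect | Not listed | Not significant | Consistent |
| Subdural 4 mm to 1.0 cm, no mass effect | Not listed | Not named | Default only |
| Epidural 1.0 cm or less, no mass effect | Not listed | Not named | Default only |
| Subarachnoid blood neither extensive nor localized and under 1 mm | Not listed; no measure for extensive | Not named | Default only |

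The last three rows are not positive by default, because the positive list is the operational rule. The protocol does not say so.

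**Step 2: the review triggers.** Positive scan in 4.2 and 4.3.5.1.2; any intracranial injury on the report in 4.3.4. The two differ for every patient with an intracranial injury that is not on the positive list. In addition, 4.3.4 covers the associated visit, while the outcome window is seven days, so an event after that visit but within the window falls outside the stated review.

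**Step 3: the protocol's own figure.** Section 3.2 sets α = 0.05, uses α/2, and takes X = N. The exact lower limit with no misses is then

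P_L = (α/2)^(1/N), so N = ln(0.025)/ln(0.99) = 367.04, rounded up to 368.

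This reproduces the stated 368. At 1.2% prevalence, 368/0.012 = 30,667, consistent with the stated 31,000.

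**Step 4: slack in the target.** Exact lower 95% limits:

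- 368 of 368: 99.00%
- 367 of 368: 98.50%
- 368 of 369 (one unfound miss added to a clean 368): 98.50%
- 368 of 370 (two added): 98.06%

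With one miss, 555 cases would be needed to bring the limit back to 99.0%. The numbers of misses here are illustrative; the protocol gives no rate.

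**Step 5: direction of bias.** Only an unfound low-risk case inflates sensitivity. An unfound case that the instrument flagged does not inflate it; it slows accrual to 368.

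**The case against.** A reader might infer that only CT-positive charts are ever reviewed, and that the patient with a 6 mm subdural would therefore never be examined for the primary outcome. The protocol does not support that.

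- Neither 4.2 nor 4.3.5.1.2 restricts review exclusively to positive scans, and 4.3.4 would open this patient's record.
- Section 4.3.5.1.2 collects the final readings of all head CTs, counts in-patient studies and reclassifies wrong initial diagnoses. A lesion that later causes mass effect becomes positive.
- Section 4.3.8.2 searches the discharge diagnoses of admitted blunt trauma patients up to three months after each study period.
- Section 4.3.9.1 adds a screen of revisits and neurosurgical trauma admissions.

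These points stand as far as they go, but the backstops are partial. The 4.3.8.2 search covers patients admitted through the emergency department, so deaths there or transfers may escape it, and it rests on the liaison's judgment. It also reads the marked leaf as showing that an intracranial injury was recorded, whereas 4.3.4 marks the leaf only for neurosurgical intervention. An operated patient with an unmarked leaf could still surface through this check.

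On the definition, the second paragraph can be read as a set of exceptions to the first, and its examples are introduced as illustrations. That is a natural reading, but no sentence states it and the any-one-finding rule points the other way. The adjudicator in 4.3.5.1.2 resolves ambiguous reports; a clear report of isolated pneumocephalus is not ambiguous.

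A reader might also try to count affected patients by subtracting the derivation cohort's 6.7% (917/13,728, section 3.1) from the top of the 5% to 18% range of abnormal scans in section 2. At the bottom of that range the difference is 5% − 6.7%, which is negative, and section 2 attributes part of the spread to differing criteria for scanning. Abnormal scans are not lost outcomes either. In the derivation data none of the 16 missed injuries needed neurosurgery.

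**Conclusion.** The point holds in this form. Section 4.3.5.1.2 classifies isolated pneumocephalus, closed depressed fractures sparing the inner table, and thin subdurals that are bilateral or in the posterior fossa in two incompatible ways, with no precedence. This bears directly on the secondary outcome. Intermediate findings fall to an unstated default. The trigger for the primary-outcome record review is stated in two ways, and the wider one covers a shorter span than the seven-day outcome.

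The protocol does not show that primary-outcome cases will be lost, only that a site following the narrower trigger could lose some and that the other checks would not reliably recover all. The size of any bias is unknown. It matters because one low-risk case, found or not, separates a limit of 99.00% from one of 98.50%, below the 99.0% target. That comparison assumes 368 neurosurgical cases, the exact two-sided 95% limit of section 3.2, and otherwise perfect detection.

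**What to change.** 1. Merge the two paragraphs of 4.3.5.1.2 into one mutually exclusive classification. State which entry prevails where two apply, give a measure for subarachnoid blood, and state the default for findings not listed.
2. Use one trigger for the neurosurgical record review: any traumatic intracranial injury on any collected report. This is in substance the 4.3.4 trigger; adding skull fracture would extend it and should be a deliberate choice.
3. State that the review covers the full seven days after injury, not only the associated visit.
4. Reconcile 4.2, 4.3.4, 4.3.5.1.2, 4.3.7 and 4.3.8.2 accordingly, including what the leaf mark means.

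The cost is protocol and abstraction-form wording, plus some additional chart checks by the existing research assistants. The change belongs before abstraction begins.
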